### Randomisation, allocation concealment and sequence generation

Callers will be told about the trial and asked if they would like to take part by a research assistant. If interested, they will be asked for basic demographic data (age, sex and ethnicity) and checked to see if they meet the trial inclusion criteria. Those who provide further details about their level of nicotine dependence (determined by the Fagerström Test for Nicotine Dependence [FTND] questionnaire [24]) will be randomised by a central computer programme to one of the three study groups using stratified block randomisation with block sizes of nine. The randomisation sequence will be prepared in advance by the study statistician (VP) but will be concealed from research assistants enrolling participants. Participants will be assigned to the 16 mg e-cigarette and nicotine patch groups in a ratio of 1:1 (290 in each) and to the nicotine e-cigarette and placebo e-cigarette groups in a ratio of 4:1 (73 in the latter arm). Three stratification factors will be used: ethnicity (Māori, Pacific, non-Māori non-Pacific), sex (male/female) and level of nicotine dependence (> 5 or ≤ 5 on the FTND [24]).

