### Sample size

A sample size of 657 people (292 in both nicotine-cigarette and nicotine patch groups and 73 in the placebo e-cigarette group) will provide 80% power at a two-sided p = 0.05 to detect an absolute difference of 10% in smoking abstinence rates between the nicotine e-cigarette and patch groups, and a difference of 15% between the nicotine and placebo e-cigarette groups. This assumes quit rates of 15% in the placebo e-cigarette group and 20% in the nicotine patch group (based on meta-analyses of NRT trials by Fiore et al. [29] and our own trials of nicotine patch [30]). This sample size allows for analysis of consistency of effects for pre-specified subgroups (e.g. Maori, non-Maori) to be assessed. Based on our previous experience we estimate recruitment will take approximately 12–15 months [31].

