### Statistical analysis

A senior biostatistician determined the sample size and wrote the statistical analysis plan agreed upon by all members of the Steering Committee specifying *a priori* all analyses to be undertaken. All statistical analyses will be performed using SAS version 9.3 (SAS Institute Inc. Cary, North Carolina, US) and R version 2.11.1 software (http://www.r-project.org). All regression analyses will be conducted for the following two comparisons: 16 mg e-cigarette versus nicotine patch groups; and 16 mg e-cigarette versus 0 mg e-cigarette groups.

No interim analyses will be undertaken. All tests of significance will be two-tailed. The primary analyses will be carried out on an intention to treat (ITT) basis. The ITT population will comprise all randomised participants regardless of whether they actually satisfied the entry criteria, the treatment was actually received and they subsequent withdrew or deviated from the protocol. The numbers discontinuing treatment prematurely for any reason will be summarised by treatment group and by reasons for discontinuation. The incidence of all suspected serious adverse treatment reactions will be summarised by treatment group in line with the CONSORT 2010 recommendations [32]. Simple incidence rates, relative and absolute risks, numbers needed to treat will be calculated for all binary variables, and the treatment groups will be compared using chi-squared tests with multiple logistic regression analysis adjusting for other variables as appropriate. The distribution of all continuous outcomes will be assessed for normality and skewed data will be subjected to an appropriate transformation before analysis. The change from baseline in physical signs and symptoms associated with withdrawal (AUTOS) [25] and number of cigarettes smoked per day will be analysed using repeated measures models adjusting for baseline value. The proportion of participants who have significantly reduced their daily smoking level (defined as reducing consumption by at least 50% in terms of numbers of cigarettes per day) will be calculated, and in users of loose tobacco, the size of pouch/package currently bought and number of days taken to smoke its contents measured. Finally, the number of other quit attempts in the last six months will be calculated.

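### The test named for six-month abstinence ignores the three factors that stratify randomisation, which costs between nothing and about 3 points of power

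*Protocol article*

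**What the plan says.** The section on randomisation in the protocol article specifies "stratified block randomisation with block sizes of nine" and lists the factors: "Three stratification factors will be used: ethnicity (Māori, Pacific, non-Māori non-Pacific), sex (male/female) and level of nicotine dependence", the last split at an FTND score of 5. That makes 3 × 2 × 2 = 12 strata.

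The Statistical analysis section covers all binary variables in one sentence, which therefore includes the primary outcome: "the treatment groups will be compared using chi-squared tests with multiple logistic regression analysis adjusting for other variables as appropriate". It applies the regressions to both hypothesis contrasts, nicotine e-cigarette against patch ("All regression analyses will be conducted for the following two comparisons: 16 mg e-cigarette versus nicotine patch groups") and nicotine against placebo e-cigarette. It does not name the stratification factors as covariates, and it does not rank the chi-squared and regression results. It refers to a separate analysis plan, agreed by the Steering Committee, that is said to fix every analysis in advance. That plan is not available here.

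**The concern.** Stratified blocks force the arms to be nearly balanced on the 12 strata. If those strata predict quitting, the difference in quit rates varies less between hypothetical repetitions of the trial than the chi-squared test assumes, because its variance is that of unrestricted randomisation. The standard error is then too large. The test rejects a true null hypothesis less often than 5% of the time, and some of the precision that stratification could buy is not used.

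At stake is a modest amount of power in two contrasts that were planned at or near 80%, and clarity about which of two possible results for the same outcome is the primary one.

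**Working it through.** **Inputs from the article.** Sample size: "A sample size of 657 people (292 in both nicotine-cigarette and nicotine patch groups and 73 in the placebo e-cigarette group". Target: "will provide 80% power at a two-sided p = 0.05 to detect an absolute difference of 10% in smoking abstinence rates", with 20% on patch and 15% on placebo e-cigarettes. Nicotine e-cigarettes are therefore at 20% + 10% = 30%, and equally 15% + 15% = 30%. Tests are two-sided.

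**The article's own figure.** With h = 2·arcsin√p₁ − 2·arcsin√p₂ and z = 1.960 + 0.842 = 2.802:

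- Patch contrast: h = 0.232, so n = 2(2.802/0.232)² ≈ 292 per arm. Power at 292 is 80.0%.
- Placebo contrast at 4:1: h = 0.364, so n = 1.25(2.802/0.364)² ≈ 74. Power at 73 against 292 is 79.4%.

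The stated sizes are thus reproduced by an unadjusted two-proportion calculation. The pooled-variance formula gives 79.8% and 76.7%. The unpooled formula gives 290.4 per arm for the patch contrast and 85.6% power for the placebo contrast.

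**Why chi-squared is conservative here.** Let R² be the share of outcome variance that the strata explain. With balance within strata, the true null variance of the difference is p(1 − p)(1 − R²)(1/n₁ + 1/n₂). Chi-squared omits the factor (1 − R²). Its type I error is therefore about 2[1 − Φ(1.96/√(1 − R²))].

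**Assumptions.** The article gives neither stratum shares nor quit rates by stratum. Assumed shares: Māori 30%, Pacific 10%, other 60%; sex 40/60%; FTND 45/55%. Assumed odds ratios for abstinence, in the order Māori, Pacific, sex, high FTND:

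- Mild: 0.8, 0.8, 0.8, 0.7 (patch-arm stratum quit rates 14–27%, R² = 0.0089)
- Moderate: 0.6, 0.6, 0.75, 0.5 (10–34%, R² = 0.0311)
- Strong: 0.4, 0.4, 0.6, 0.33 (6–43%, R² = 0.0812)

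The formula then gives, at a 20% quit rate:

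- Mild: 1.96/√0.9911 = 1.969, type I error 4.9%
- Moderate: 1.96/√0.9689 = 1.991, type I error 4.6%
- Strong: 1.96/√0.9188 = 2.045, type I error 4.1%

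**Simulation.** 100,000 runs, allocation balanced within the 12 strata, Pearson chi-squared against Cochran-Mantel-Haenszel (CMH). Monte Carlo standard error is about 0.07 point for type I error, √(0.05 × 0.95/100,000), and 0.13 point for power, √(0.8 × 0.2/100,000).

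| Stratum effects | Contrast | Type I %, chi-squared / CMH | Power %, chi-squared / CMH | Gain, points |
|---|---|---|---|---|
| None | Patch | 4.99 / 4.96 | 79.6 / 79.6 | 0.0 |
| None | Placebo | 5.09 / 5.07 | 77.2 / 77.0 | −0.2 |
| Mild | Patch | 4.90 / 4.97 | 80.3 / 80.5 | 0.2 |
| Mild | Placebo | 4.91 / 4.95 | 77.6 / 77.7 | 0.2 |
| Moderate | Patch | 4.64 / 4.94 | 80.6 / 81.5 | 0.9 |
| Moderate | Placebo | 4.61 / 4.87 | 77.6 / 78.6 | 1.0 |
| Strong | Patch | 4.04 / 4.90 | 81.0 / 83.6 | 2.6 |
| Strong | Placebo | 4.22 / 4.89 | 78.3 / 81.2 | 2.9 |

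Gains are taken before rounding. The patch type I errors agree with the formula. A main-effects logistic regression with a Wald test (8,000 runs) gives similar gains. At moderate effects, power goes from 79.4% to 80.6% for patch and from 77.6% to 78.5% for placebo. At strong effects it goes from 80.9% to 83.6% and from 77.3% to 80.3%. A further simulation with actual blocks of nine at 4:4:1 (40,000 runs) shows the same pattern: no difference without prognostic effects, about 1 point at moderate effects and 2.5 to 3 points at strong effects.

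**The case against.** The strongest reply is that an adjusted logistic regression is already planned for both contrasts, that its covariate list belongs in the analysis plan, and that the planned power does not depend on adjustment. Much of this stands. An unlisted covariate set in an article is not by itself a fault, and the sample size does reproduce without adjustment. An unadjusted test also sits naturally with the risk differences and NNTs that the article promises. What survives is that the article does make a choice: it names a test that does not match the allocation scheme, and it ties the accompanying model neither to the stratification factors nor to the primary result.

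A reader might infer four stronger things, and the documents support none of them.

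- **That no adjusted analysis is planned.** The quoted sentence includes one.
- **That the covariates could be picked after unblinding.** The article cites a plan fixed in advance. Its Blinding section keeps everyone except the co-ordinator and research assistants blind until the last follow-up is recorded.
- **That the placebo contrast is already short of power.** This depends on the formula: 76.7% pooled, 79.4% arcsine, 85.6% unpooled.
- **That adjustment gains 3 points or more in the placebo contrast even at moderate effects.** Comparing Pearson chi-squared with an adjusted likelihood-ratio test suggests this, but it changes the statistic as well as the adjustment. With no stratum effect at all, that comparison still moves placebo power from 77.4% to 79.7% (8,000 runs), a gain of 2.3 points unrelated to the strata.

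**Conclusion.** The point holds as a modest, nearly free improvement. The chi-squared test is valid and there is no type I error inflation. If the stratification factors predict quitting, the test is mildly conservative, with type I error of about 4.0% to 5.0% over the range tried. Against a stratified test it then gives up about 1 point of power at moderate effects and up to about 3 points at strong effects, in both contrasts. If the factors are not prognostic, nothing is lost. The direction follows from the design. The size rests entirely on assumed stratum shares and odds ratios, because the article reports none.

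**What to change.** For both contrasts, state that the primary test of six-month abstinence accounts for the three stratification factors. Two forms would serve:

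- a Cochran-Mantel-Haenszel test over the 12 strata; or
- a logistic regression with ethnicity (three levels), sex and FTND (>5 / ≤5) as main effects, with the test statistic named in advance, since Wald and likelihood-ratio tests can differ under 4:1 allocation.

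The placebo arm averages only 73/12 ≈ 6 people per stratum, so main effects are preferable to a full set of stratum terms if the regression is chosen.

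Report the risk difference and NNT standardised over the strata, and keep the unadjusted chi-squared test as supportive. If the separate analysis plan already does this, the article's Statistical analysis section should say so.

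The cost is a change of wording. The factors are recorded before randomisation, so no new data or participants are needed. The one small downside is that the marginal risk difference must be obtained by standardisation or stratum weighting instead of read from the raw proportions.

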### Cost effectiveness analysis

If the primary outcome of the trial is positive then cost analyses will be undertaken. Cost outcomes will include cost per quitter, cost per person reducing their daily cigarette consumption and incremental cost-effectiveness ratio. These data will then be compared with data from the NZ Quitline and other cessation service providers, in addition to information from various international studies, using a health sector perspective. The tobacco expenditure savings to smokers who quit or cut down will also be calculated, especially to low-income smokers, using data on the daily amount smoked prior to quitting and the price of the products smoked. For those who cut down daily consumption by 25% or more, the cost savings per person reducing their daily cigarette consumption will be calculated.

### Ethical considerations

Ethics approval was granted from the New Zealand Ministry of Health’s Northern Ethics Committee (Ethics number NTX/10/11/111). Verbal consent will be obtained at the time of contact with the research team. However, a written consent form and patient information sheet will be posted to participants for their information, requesting that they send it back to the study centre in a pre-paid envelope, once signed. All data will be entered, stored and backed-up in a secure manner via a password-protected data management system. Participants will be acknowledged in all publications and presentation of the results.

## Discussion

There are many challenges with the design of this study. A key issue is that of intervention product selection. There is a large and growing number and diversity of e-cigarette products on the market, with only limited evidence available on their performance and quality. E-cigarettes differ in their characteristics such as the ability to deliver vapour reliably, the concentration of nicotine in the solution, flavour and other additives, and amount of vapour produced [31]. These differences may impact on the efficacy and acceptability of a particular brand or model so it is possible that different trial findings may be obtained using other brands or models of e-cigarette. Furthermore, e-cigarettes are evolving rapidly and a brand tested in a trial may no longer be on the market by the time the study is completed and results published.

We chose to use a particular brand (Elusion™) and model of e-cigarette for three reasons: its wide availability and popularity in New Zealand and Australia in 2011; we were able to obtain good evidence of the quality of cartridge solution production; and it was made available to us at no cost by the distributor without restrictions.

The choice of a ‘usual care’ comparator was not straightforward. We elected to use the 21 mg nicotine patch, by far the most widely used NRT product in New Zealand. Patch use will also enable us to assess whether any excess of adverse outcomes is due to the e-cigarette. The alternative comparator most seriously considered was the medicinal nicotine inhaler because of its similar use characteristics to e-cigarettes (oral inhalation, on demand use, use of hands to apply). However, it is not subsidised in NZ and to include it would have added substantial cost; also its use is aversive to start with and so a barrier for many people [33]. We chose a three-arm design with a placebo e-cigarette arm to answer the question of whether any observed efficacy could be due to behavioural replacement alone.

Users report needing time to familiarise themselves with e-cigarettes to get satisfaction [21,32], and studies that have reported some of the highest blood nicotine levels associated with e-cigarette use were undertaken in experienced users [33]. We have attempted to address this by providing participants with detailed illustrated instructions of how to use e-cigarettes, and requiring that they try them for a week prior to embarking on their quitting attempt.

The trial will report on clinical efficacy and adverse effects over a six month period of observation. This follow-up period is sufficient to determine if smokers are assisted to quit and to see if the use of nicotine e-cigarettes leads to an excess of adverse effects after eight week’s use over and above placebo e-cigarettes or nicotine patch. The results will make a valuable contribution to the Cochrane Systematic Review on electronic cigarettes for smoking cessation and reduction [34].

The study does not address the safety of long-term use of e-cigarettes (beyond 13 weeks). Neither will the study address the role of e-cigarettes as a ‘gateway’ product to tobacco smoking or a trigger to relapse to tobacco smoking. To answer these questions will require other studies using different designs.

Finally, our study will not provide a definitive answer to address all e-cigarette regulation issues. However, should the findings be in favour of nicotine e-cigarettes without additional adverse effects then it will establish a new balance between clinical benefit and harm for three month’s use of e-cigarettes.

## Abbreviations

FTND: Fagerström test for nicotine dependence; NIHI: National Institute for Health Innovation; NZ: New Zealand.

## Current status

The trial started recruiting participants in August 2011. Trial findings are likely to be available in September 2013.
